The data from the United States have shown that less than one-third of at-risk adults receive any vaccination for Hep A, and only one-fifth receive both doses [2,9-12]. Adherence to the vaccination schedule was worse at the extremes of adult age, in ethnic minorities, and in those of low socioeconomic status [10]. The same is true in the United Kingdom; under 35% of eligible people receive the complete Hep A vaccination course, though these data are presented for all eligible patients, regardless of CLD status [13].

Hence, there are no published reports of Hep A vaccination coverage in people with CLD. The purpose of this study is to report Hep A vaccine coverage in people with CLD in UK primary care, with a focus on whether there are disparities as to which people with CLD receive Hep A vaccination.

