### Variables

#### Overview

The study population is those with CLD as an index condition, as defined in the inclusion criteria. The variables will be curated for the identification of CLD-related codes in the computerized medical records of adults registered in the RSC network (Multimedia Appendix 1).

Comparisons will be conducted between population subgroups with different CLD etiologies, sociodemographic characteristics, complications, and comorbidity profiles.

The outcome of the first objective will be the coverage rates of Hep A vaccination among those with CLD.

For the second objective, we will explore significant independent predictors of the following outcomes among those with CLD: (1) one dose of Hep A vaccination and (2) two doses of Hep A vaccination.

Hep A vaccination, as defined by the UK vaccination scheme, includes an initial 0.5 mL for 1 dose, followed by a booster dose of 0.5 mL after 6-12 months. The booster dose may be delayed by up to 3 years if not given after the recommended interval following the primary dose [8]. For this study, we will report boosters administered within 12 months of the first dose for the base case analysis and 3 years from the first dose for a sensitivity analysis. Hep A vaccination in the United Kingdom is available as a monovalent vaccine, as a combined Hep A and hepatitis B vaccine, and as a Hep A and typhoid vaccine [7]. We will consider any Hep A vaccination type as an outcome.

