#### Reporting Predictors of 1 and 2 Doses of Hep A Vaccination in People With CLD

##### Overview

A multistate model will be used on a retrospective cohort of individuals identified in the ORCHID diagnosed with CLD. People enter the study on the first diagnosis of CLD, and we will model the transition probabilities between the identified states: diagnosed with CLD, first dose of Hep A vaccination, second dose of Hep A vaccination, and death (Figure 2).

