**Figure 2 figure2:**

State transition diagram for competing risks multistate model for a retrospective cohort of adults with chronic liver disease (CLD) in England between January 1, 2012, and December 31, 2022, evaluating hepatitis A (Hep A) vaccination with 1 and 2 doses as outcomes and death as a competing risk represented as an absorbing state.

A multistate survival model will be fitted to estimate the transition probabilities between the 4 identified study states (Figure 2). The states are (1) diagnosis of CLD, (2) first dose of Hep A vaccination, (3) death, and (4) second dose of Hep A vaccination. The outcome of interest is the Hep A vaccination. Therefore, the state of a second dose of Hep A vaccination is a censored state, with no further transitions to death; the moment a patient receives 2 doses of Hep A vaccination, the follow-up ends. Death is an absorbing state, with no further transitions allowed. Death is included as a competing risk for vaccination, not as an outcome. This means that when calculating the transition probabilities to vaccination, we adjust for when a person is not vaccinated because of death before vaccination rather than for any other predictors of nonvaccination.

Patients lost to follow-up will be right censored and evaluated accordingly as per the likelihood function of the “msm” R package [30].

Multistate probabilities are based on the same assumptions as a Markov process:

The health states considered in the model are thorough and mutually exclusive.The probability to move from one health state to following states only depends on (is conditioned on) the health state of the individual at transition time (memoryless process).Transition probabilities are steady over time.

The state transition probabilities will be estimated conditional on the study risk factors. Study risk factors include (1) etiology of CLD (eg, ALD, CH-B, CH-C, and NAFLD); (2) sociodemographic characteristics (eg, age, sex, ethnicity, deprivation, obesity, smoking, and alcohol consumption); (3) CLD complications (eg, bile duct and colon cancers, renal disease, ascites, liver failure and transplant, and cardiometabolic disease); and (4) comorbidities (eg, CMMS, bile duct and colon cancers, at least 3 doses of COVID-19 vaccine, and flu vaccination).

The multistate model will be estimated using the “msm” (version 1.6.9) package in R [31].

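### For the one-dose outcome the plan names only multistate transition probabilities; read literally, these drop people who complete the course, so groups that complete faster can look less likely to get a first dose

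*Protocol article*

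**What the plan says.** Under Variables, Overview, the article sets two outcomes for the second objective: "1) one dose of Hep A vaccination and (2) two doses of Hep A vaccination". It does not say whether one dose means at least one or exactly one.

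The section on reporting predictors of 1 and 2 doses assigns these outcomes to a multistate model. Its Overview says that "we will model the transition probabilities between the identified states". The text with Figure 2 lists them: "The states are (1) diagnosis of CLD, (2) first dose of Hep A vaccination, (3) death, and (4) second dose of Hep A vaccination". It then states three things that matter here:

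- On the states: "The health states considered in the model are thorough and mutually exclusive".
- On the second dose: "the moment a patient receives 2 doses of Hep A vaccination, the follow-up ends".
- On covariates: "The state transition probabilities will be estimated conditional on the study risk factors".

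The same text assumes a memoryless process with constant transitions, fitted with the msm package in R. It names no hazard ratio, cumulative incidence, first-entry probability or time horizon. Under Sensitivity Analysis, two models are planned that differ only in the window for dose 2: 1 year or 3 years after dose 1.

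**The concern.** In a multistate model, the transition probability from state 1 to state 2 over time t is the chance of being in state 2 at t. That equals the chance of ever having entered state 2 only if nobody leaves it. Here the first-dose state is transient, because completing the course moves a person to the second-dose state.

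The one output the article names therefore does not measure receipt of a first dose. It mixes how readily a group starts vaccination with how slowly it finishes. A characteristic that speeds completion lowers the figure even when first-dose uptake is equal or higher.

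The second objective exists to find disparities, and the Discussion intends to use them to target interventions. The Introduction reports that in US data adherence to the schedule differed by age, ethnicity and socioeconomic status, so differences in completion between the groups of interest are to be expected.

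**Working it through.** The article states no transition probability, so there is no figure to reproduce. The check is an illustration.

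**Inputs.** From the article: the four states, constant intensities, dose 2 as the end of follow-up, and dose-2 windows of 1 and 3 years. Assumed: *a* = rate of CLD to dose 1, *b* = rate of dose 1 to dose 2, *d* = 0.04 per year death rate from either of the first two states, and *t* = 5 years. Group A starts and completes faster (*a* = 0.10, *b* = 1.0 per year). Group B starts and completes more slowly (*a* = 0.07, *b* = 0.25 per year).

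**True first-dose uptake** (cumulative incidence of first entry, death before dose 1 competing): F = a/(a+d) × [1 − exp(−(a+d)t)].
- A: 0.10/0.14 × (1 − e^−0.70) = 36.0%
- B: 0.07/0.11 × (1 − e^−0.55) = 26.9%

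**Literal transition probability, no limit on dose-2 timing:** P = a/(b−a) × e^(−dt) × [e^(−at) − e^(−bt)].
- A: 0.10/0.90 × 0.8187 × (0.6065 − 0.0067) = 5.5%
- B: 0.07/0.18 × 0.8187 × (0.7047 − 0.2865) = 13.3%

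**Same quantity when dose 2 counts only within *w* years of dose 1** (later completers stay in the first-dose state): P = e^(−dt) × { e^(−bw)[1 − e^(−a(t−w))] + a e^(−at)[1 − e^(−(b−a)w)]/(b−a) }.

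| | True uptake | No limit | w = 1 year (base case) | w = 3 years (sensitivity) |
|---|---|---|---|---|
| A | 36.0% | 5.5% | 13.2% | 5.9% |
| B | 26.9% | 13.3% | 19.3% | 14.4% |

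For w = 1, A is 0.8187 × (0.1213 + 0.0400) and B is 0.8187 × (0.1902 + 0.0451). For w = 3, A is 0.8187 × (0.0090 + 0.0629) and B is 0.8187 × (0.0617 + 0.1144). The ranking is reversed in every column. The figure also moves between the two planned models although the dose-1 data are identical in both.

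**Equal starters.** With *a* = 0.085 in both groups, true uptake is 31.6% in each. The unlimited-window probability is 4.9% for *b* = 1.0 and 15.5% for *b* = 0.25.

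**Role of death after dose 1.** With no deaths after dose 1, the first pair gives 5.7% against 14.5%. Loss to dose 2 alone produces the reversal.

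**Role of the horizon.** For the first pair the two probabilities tie at 1 year (5.7% each) and are reversed at 2 years (7.0% against 9.4%, no limit). In a second example (death 0.03 per year; true 10-year uptake 50% and 30%; completion rates 1.0 and 0.05 per year) there is no reversal at 1 year (4.9% against 3.9%), but there is at 3 years (6.1% against 10.1%).

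**What is not distorted.** In that second example, with 200,000 simulated people per group, the CLD-to-dose-1 intensities were recovered: 0.084 against a true 0.084, and 0.042 against a true 0.042. Ratios of this intensity do not depend on the completion rate.

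**The case against.** The strongest reply is that the article never says first-dose uptake will be read from occupancy of the first-dose state. That is correct. A reader might infer that uptake is derived this way, but the text does not go that far. The wording about moving between states with constant probabilities fits a rate better than an occupancy probability, which changes with t. The sentence on adjusting for death before vaccination is close to first-entry incidence. The Limitations section calls the model time-to-event modelling, and msm can give undistorted intensity ratios. A condensed article may also leave model summaries to a fuller plan.

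Much of this stands, and it limits the point to what follows if the named output is used as written. It does not remove the point. The article itself chose the output and the state structure, and together they give the wrong quantity for one of its own outcomes.

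Three stronger readings are not supported:

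- **That reported coverage, or its comparison with US rates, is compromised.** Under Statistical Analysis, coverage is a direct count over the CLD population and does not come from the model.
- **That the single death state is an error that must be split.** Figure 2 is not available here, so a path from dose 1 to death cannot be confirmed; the text rules out death only after dose 2. First-entry incidence needs only the two intensities out of the CLD state.
- **That the size of the distortion is known.** The rates, the horizon and the fourfold difference in completion are assumptions.

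**Conclusion.** The point holds in conditional form. If the stated transition probabilities are used for the one-dose outcome, they measure being alive with exactly one dose, and comparisons between groups can be understated or reversed. In the illustration, a true difference of 9.1 points in favour of group A (36.0 − 26.9) becomes 7.8 points against it with no limit on dose 2 (13.3 − 5.5), or 6.1 points against it with the 12-month window (19.3 − 13.2). Reversal needs a sizeable difference in completion and, in these examples, a horizon beyond about 1 year. The study window is 11 years and the article fixes no horizon. This is more than missing detail, but it is confined to model-based probabilities for the one-dose outcome of the second objective.

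**What to change.** Under Variables, Overview, and in the text with Figure 2:

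1. Define one dose as at least one dose.
2. Base its predictors on the hazard (intensity) ratios for the CLD-to-dose-1 transition, and on the cumulative incidence of first entry to dose 1 at a stated horizon, with death before dose 1 as the competing event. State that occupancy of the first-dose state is not used for this outcome.
3. Define the full-course outcome as the cumulative incidence of entry to the second-dose state.

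Splitting death into before and after dose 1 is optional. It matters only if at least one dose is built by summing state probabilities, where deaths after dose 1 would otherwise be missed.

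The cost is a few sentences and one extra reported quantity. The data do not change, and the new outputs come from the same fitted model.

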**Methods:**

We will conduct a retrospective cohort study with data from the Primary Care Sentinel Cohort of the Oxford-Royal College of General Practitioners Clinical Informatics Digital Hub database, which is nationally representative of the English population. We will include people aged 18 years and older who have been registered in general practices in the Research and Surveillance Centre network and have a record of CLD between January 1, 2012, and December 31, 2022, including those with alcohol-related liver disease, chronic hepatitis B, chronic hepatitis C, nonalcohol fatty liver disease, Wilson disease, hemochromatosis, and autoimmune hepatitis. We will carefully curate variables using the Systematized Nomenclature of Medicine Clinical Terms. We will report the sociodemographic characteristics of those who are vaccinated. These include age, gender, ethnicity, population density, region, socioeconomic status (measured using the index of multiple deprivation), obesity, alcohol consumption, and smoking. Hepatitis A vaccination coverage for 1 and 2 doses will be calculated using an estimate of the CLD population as the denominator. We will analyze the baseline characteristics using descriptive statistics, including measures of dispersion. Pairwise comparisons of case-mix characteristics, comorbidities, and complications will be reported according to vaccination status. A multistate survival model will be fitted to estimate the transition probabilities among four states: (1) diagnosed with CLD, (2) first dose of hepatitis A vaccination, (3) second dose of hepatitis A vaccination, and (4) death. This will identify any potential disparities in how people with CLD get vaccinated.

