## Discussion

### Overview

This study will inform on the state of preventive Hep A vaccination for people with CLD in a representative primary care sentinel network in England. From a total of 7.4 million patients in the RSC network, we will report on the sociodemographic and clinical characteristics of people with CLD with and without Hep A vaccination, for 1 and 2 doses.

The multistate model, adjusted for study risk factors, will identify those associated with having the vaccination. This will inform on the individual characteristics that are associated with an immunization, informing on the subgroups that could benefit from higher engagement with preventive primary care. Any disparities identified could be used to target clinical and public health interventions to improve vaccination coverage in this at-risk group.

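### The multistate model used to identify disparities adjusts ethnicity and deprivation for flu and COVID-19 vaccination, complications and comorbidity, so its social coefficients can understate the overall gap

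*Protocol article*

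**What the plan says.** In Methods, Statistical Analysis, the text under Figure 2 states: "The state transition probabilities will be estimated conditional on the study risk factors". The factors form one list in four groups. The social factors are in the second: "2) sociodemographic characteristics (eg, age, sex, ethnicity, deprivation, obesity, smoking, and alcohol consumption". The third is "3) CLD complications (eg, bile duct and colon cancers, renal disease, ascites, liver failure and transplant, and cardiometabolic disease". The fourth is "4) comorbidities (eg, CMMS, bile duct and colon cancers, at least 3 doses of COVID-19 vaccine, and flu vaccination". No smaller covariate set and no order of fitting is given. The Sensitivity Analysis section plans two multistate models, but they differ only in the time window allowed for dose 2.

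The article also says what the model is for. In the Abstract (Methods), directly after the multistate model is described: "This will identify any potential disparities in how people with CLD get vaccinated". In the Discussion (Overview): "The multistate model, adjusted for study risk factors, will identify those associated with having the vaccination"; the same section says that disparities found could steer clinical and public health action. The Introduction gives the study's purpose as reporting coverage, "with a focus on whether there are disparities as to which people with CLD receive Hep A vaccination".

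Separately, the first objective reports yearly coverage by sociodemographic group, and the coverage analysis compares characteristics by vaccination status with unadjusted tests.

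**The concern.** Flu and COVID-19 vaccination are filed under comorbidities, but they are not case mix. They reflect access to, and acceptance of, vaccination, which is a likely route by which a deprived or minority group misses the hepatitis A vaccine. A deprivation coefficient adjusted for them asks whether deprived patients are vaccinated less than other patients with the same uptake of other vaccines. The Introduction asks something wider: whether some groups are vaccinated less. Complications and the Cambridge Multimorbidity Score raise the same difficulty less sharply, since health at diagnosis may itself follow from social position. Dating these covariates correctly before CLD diagnosis would not remove the problem.

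At stake is the reading of a null result. A group that is under-vaccinated because it is poorly reached by vaccination in general could show little or no adjusted effect, and so drop out of the groups considered for targeting.

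**Working it through.** The plan gives no effect size on this point, so there is no figure of its own to reproduce. The check has two parts.

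**1. What the text fixes**

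- Covariates: ethnicity, deprivation, complications, multimorbidity score, flu vaccination and COVID-19 vaccination, all in one conditioning list (text under Figure 2).
- Variants of the model: two, differing in the dose 2 window only (Sensitivity Analysis).
- Use: identification of disparities (Abstract, Methods) and of factors associated with vaccination (Discussion, Overview).
- Reason for adjusting: control of confounding by case mix (Limitations). Mediation is not mentioned.

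The disparity reading is therefore attached to coefficients conditional on possible mediators, and no model without them is named.

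**2. How much this could matter (all inputs assumed)**

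Let p0 and p1 be flu vaccine uptake in the less and more deprived groups, r the rate ratio for hepatitis A vaccination in flu-vaccinated versus other patients, and d a direct effect of deprivation. At the start of follow-up:

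- overall ratio = d × (p1·r + 1 − p1) / (p0·r + 1 − p0)
- ratio adjusted for flu vaccination = d

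| p0 | p1 | r | d | Overall | Adjusted |
|---|---|---|---|---|---|
| 0.60 | 0.40 | 3 | 1.00 | 1.8/2.2 = 0.82 | 1.00 |
| 0.60 | 0.40 | 3 | 0.85 | 0.85 × 0.818 = 0.70 | 0.85 |
| 0.60 | 0.50 | 2 | 1.00 | 1.5/1.6 = 0.94 | 1.00 |

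In the second row the share of the log ratio removed is 1 − ln(0.85)/ln(0.695) = 1 − 0.163/0.364 = 0.55.

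A separate simulation used 400,000 patients, a base rate of 0.05 per year, 5 years of follow-up, uptake of 70% versus 40% to 60%, and r from 1.5 to 3:

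| d | Hazard ratio without uptake | With uptake | Share of log ratio removed |
|---|---|---|---|
| 1.00 | 0.74 to 0.97 | about 1.00 | all |
| 0.85 | 0.63 to 0.82 | about 0.85 | 20% to 65% |
| 0.70 | 0.52 to 0.67 | about 0.70 | 9% to 44% |

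If flu vaccination is only a noisy marker of access, less is lost. A simulation of 1,000,000 patients with a latent access variable, death and censoring gave 0.668 to 0.674 without flu vaccination and 0.714 to 0.752 with it. The share removed runs from 1 − ln(0.714)/ln(0.674) = 0.15 to 1 − ln(0.752)/ln(0.668) = 0.29.

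The direction is the same throughout: adjustment moves the social ratio towards 1. How far depends on how much of the gap runs through the adjusted variables.

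**The case against.** The strongest reply is that disparities are not read from this model alone. The first objective reports coverage by ethnicity and deprivation, the coverage analysis compares groups without adjustment, and the Conclusions link disparities to describing uptake. A gap working through vaccine access would show there. This stands, and a reader who inferred that the plan would hide such a gap altogether would go too far. But no age or sex adjustment and no handling of death is stated for those results, and the Abstract and Discussion give the task of identifying disparities to the adjusted model. If a crude gap shrinks in that model, nothing in the article says that the two results answer different questions.

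A second reply is that the second objective seeks independent predictors, that mutual adjustment is what independent means, and that the vaccines are named as exposures of interest. This justifies keeping the full model. It does not make its social coefficients the measure of disparity.

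A third is that the lists are examples and a fuller plan may stage the fitting. That is possible. But the two vaccine covariates are named outright, and so is the use made of the model.

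A reader might also extend the point to etiology, because ALD is entered beside alcohol consumption and NAFLD beside obesity. The document does not support that. Drinking comes before ALD, and the Introduction associates NAFLD with metabolic syndrome and obesity, so these act as confounders rather than mediators. Suppose heavy drinking halves the vaccination rate and is present in 85% of ALD and 10% of other patients. The crude ALD ratio is (0.85 × 0.5 + 0.15)/(0.10 × 0.5 + 0.90) = 0.575/0.95 = 0.61 and the adjusted ratio is 1.0. Since ALD has no effect of its own in this example, 1.0 is the right confounder-adjusted answer.

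**Conclusion.** The point holds for ethnicity and deprivation. The adjusted coefficients measure gaps at equal uptake of other vaccines and equal recorded health, and can understate the overall disparity that the Abstract and Discussion say the model will identify.

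The size is unknown. On assumed inputs it runs from about 9% of the log ratio, with a strong direct effect and weak mediation, to the whole of it when the gap works entirely through uptake; with uptake as a noisy marker it is about 15% to 29%. It would be tempting to say that the disparity is adjusted away. That is true only of the part that passes through the adjusted variables, and the document gives no means of sizing that part. The conclusion rests on the premise that uptake of other vaccines shares causes with hepatitis A vaccination and differs by social group. That is plausible, but the article gives no data on it.

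The point merits a change because the results are meant to inform targeting and the change is cheap.

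**What to change.** In the text under Figure 2, state that the multistate model will be fitted in stages:

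1. Age, sex and ethnicity. The ethnicity gap is read here.
2. The same with deprivation added. The deprivation gap is read here.
3. The full risk-factor list, as the explanatory analysis of independent predictors.

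Stages 1 and 2 leave out flu and COVID-19 vaccination, complications and the multimorbidity score. Ethnicity is read before deprivation enters, because deprivation may itself lie on the path from ethnicity to vaccination.

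Reword the disparity sentences in the Abstract and the Discussion so that disparities are read from stages 1 and 2 beside the coverage results of the first objective, and full-model coefficients are described as gaps at equal values of the other factors. The treatment of etiology needs no change on this account.

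The cost is two further covariate sets for the same model on data already extracted, a few sentences of text, and more results to report.

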### Objectives

The objectives of this study are as follows:

To report yearly Hep A vaccination coverage in people with CLD by:sociodemographic characteristics (eg, age, sex, ethnicity, deprivation, BMI category, smoking status, and alcohol consumption)etiology of CLD (eg, ALD, CH-B, CH-C, and NAFLD).CLD complications (eg, renal disease, ascites, liver failure and transplant, and other cardiometabolic diseases, including diabetes and heart disease)comorbidities and exposures (eg, Cambridge Multimorbidity Score [CMMS], bile duct and colon cancers, at least three doses of COVID-19 vaccine, and flu vaccination).To report the predictors of 1 and 2 doses of Hep A vaccination in people with CLD.

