## Methods

### Study Design

This is a retrospective cohort study using data from the nationally representative Primary Care Sentinel Cohort (PCSC) of the Oxford-Royal College of General Practitioners (RCGP) Research and Surveillance Centre (RSC) [14]. The RSC is one of Europe’s oldest sentinel systems, and hepatitis is one of its 32 monitored conditions [15]. The database has previously been used for liver disease and hepatitis research [3,16].

We will use electronic health record data for the period between January 1, 2012, and December 31, 2022. Data will be extracted retrospectively at the time of the beginning of the study.

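### Having at least 3 COVID-19 vaccine doses is an unsuitable predictor in a model that starts at CLD diagnosis in 2012-2022: coded as ever recorded, it marks survival to late in the study

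*Protocol article*

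**What the plan says.** Study Design sets the data window: "We will use electronic health record data for the period between January 1, 2012, and December 31, 2022". The Overview of the predictors analysis sets time zero: "People enter the study on the first diagnosis of CLD". The text under Figure 2 states that "The state transition probabilities will be estimated conditional on the study risk factors", and the last group of those factors is "4) comorbidities (eg, CMMS, bile duct and colon cancers, at least 3 doses of COVID-19 vaccine, and flu vaccination". The Objectives list the same items, "at least three doses of COVID-19 vaccine, and flu vaccination", among the characteristics by which yearly coverage will be reported.

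The Covariates section anchors sociodemographic variables at the earliest CLD diagnosis and takes comorbidities and complications from 10 years of records. It mentions neither COVID-19 nor flu vaccination. Nothing elsewhere dates these two items, makes them time-dependent, or limits them to years in which they could occur.

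Two further statements under Figure 2 matter here. On the competing event: "Death is included as a competing risk for vaccination, not as an outcome". Among the model assumptions: "Transition probabilities are steady over time". Follow-up also ends at the second hepatitis A dose.

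**The concern.** The name of the disease dates it to 2019. Assuming that no 3-dose course was possible before 2020, the covariate cannot be positive in at least 8 of the 11 study years (2012-2019). For most entrants it describes something that happens, if at all, years after time zero.

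If it is coded as ever recorded, only people who were still alive and registered late in the study can be positive. Everyone who died or left earlier is negative by construction. A person who completed the hepatitis A course in 2014 would be classified by an event long after leaving the model. This is immortal-time bias.

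Death competes with vaccination, so a false death rate carries into the vaccination probabilities that the study will report. The Discussion intends to use the resulting associations to identify groups for targeted engagement. In the yearly tables, coverage for 2012-2019 would be split by an event that had not yet happened.

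**Working it through.** The plan gives no figure of its own on this point, so the check takes each possible coding in turn, under a null in which COVID-19 vaccination has no effect on hepatitis A vaccination or death.

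**Inputs from the article.** Entry at first CLD diagnosis, 2012-2022 (11 years); constant transition rates; death as a competing risk.

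**Assumptions not in the article.** Entry uniform over the window; first-dose rate 5% per year; death 6% per year (range 3-10%); deregistration 5% per year; third doses given from October 2021 to mid-2022 in 70% of those still registered.

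**Coding 1: ever recorded.** Rates are events divided by person-time from diagnosis, by the fixed flag (600,000 simulated people).

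| | 3 doses | Not 3 doses | Truth |
|---|---|---|---|
| First-dose rate per year | 0.050 | 0.050 | 0.050 |
| Death rate per year | 0.010 | 0.111 | 0.060 |

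Death rate ratio: 0.010/0.111 = 0.09, where the truth is 1. With death at 3-10% per year it is 0.08-0.11. First-dose rate ratio: 1.0.

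With first-dose rate l and death rate m, the probability of a first dose by time t is l/(l+m) × (1 − exp(−t(l+m))).

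- 10 years, 3 doses: 0.05/0.060 × (1 − exp(−0.60)) = 37.6%
- 10 years, not 3 doses: 0.05/0.161 × (1 − exp(−1.61)) = 24.9%
- 10 years, truth: 0.05/0.110 × (1 − exp(−1.10)) = 30.3%
- 5 years, same formula: 21.6% against 17.2%, truth 19.2%
- 3 years: 13.7% against 11.9%
- 1 year: 4.9% against 4.6%

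With death at 3% per year the 10-year gap is about 39% against 30%; at 10% it is about 36% against 20%. The crude odds ratio for any hepatitis A dose is 1.3-1.4.

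A second simulation with different assumptions (first dose 6% per year, death 5% per year, no deregistration in the base case) agrees. Its death rate ratio is 0.075 (0.04-0.13 across scenarios), and its 10-year first-dose probability is 43.6% against 28.4%, truth 36.4%. Its first-dose rate ratio is about 1.00 in the base case. It moves to 0.77-1.18, in either direction, if death rates differ before and after the first dose or if vaccination rates change over time.

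**Coding 2: status at diagnosis.** If third doses start at 2021.75, then (2021.75 − 2012)/11 = 89% of entrants are diagnosed too early to be positive. Start dates of 2021.0 and 2022.0 give 9/11 = 82% and 10/11 = 91%. In the second simulation about 6% of entrants can be positive (5-11%). The variable then mainly marks year of diagnosis.

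**Coding 3: time-updated.** The false death effect disappears (rate ratio 0.98-1.02). The first-dose rate ratio can still be 0.79-1.18 under the null when hepatitis A vaccination rates change with calendar time or time since diagnosis, because the model assumes steady rates and names no calendar term. Restricting the comparison to calendar time after rollout as well gives 0.98-1.02 for the first dose and 0.98-1.06 for death.

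**The case against.** The strongest reply is that the article never says the variable is fixed or coded ever/never. It appears in an illustrative list, covariate timing is often left to a fuller plan, and the msm package can take time-dependent covariates. That is fair as far as it goes: ever/never coding is the natural reading but not a stated one. It does not dispose of the point, because each coding that the list allows is faulty within the model as described. The problem is the choice of predictor rather than a missing detail.

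A reader might infer that the variable directly biases the estimated effect on hepatitis A vaccination. The calculation does not support that in general. With constant rates, and equal death rates before and after the first dose, the first-dose rate ratio is about 1.0; the false gap in probability comes through the death rate. The gap also depends on the horizon, which the article does not fix. Mean potential follow-up under uniform entry is at most 11/2 = 5.5 years, so the 5-year figures are closer to typical follow-up than the 10-year ones.

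A reader might also put flu vaccination on the same footing. It does not mark survival into the COVID-19 era. If coded ever/never it accumulates with follow-up and so carries a bias of the same kind, but the size depends on the coding. One null calculation gave a crude odds ratio of about 2.7, but it rests on a single assumed rate of first flu vaccination (30% per year) and is not a multistate estimate.

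Finally, the study is descriptive and disclaims causal inference, and overall one- and two-dose coverage is unaffected. Both are true. The objective on predictors and the yearly breakdown by this item are still affected.

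**Conclusion.** The point holds for the COVID-19 vaccine item. Coded as ever recorded, it produces a large false difference in death (rate ratio about 0.08-0.11 under the null) and, through it, a false difference in first-dose probability: about 38% against 25% at 10 years and 22% against 17% at 5 years with death at 6% per year. Rollout date, uptake and event rates are assumptions. The false death difference persisted in every scenario tried. Coded as status at diagnosis, the item is largely a proxy for diagnosis year; time-updated without a calendar term, it can be confounded with calendar time.

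Two stronger readings are not supported. The first-dose rate ratio is not shown to be biased when rates are constant. And although one might expect the coefficients of age, deprivation or ethnicity to be distorted too, nothing in the article or in these calculations quantifies that, so it is not claimed. For flu vaccination the conclusion is only that its timing must be defined, since the bias depends on the coding.

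**What to change.** Remove the COVID-19 vaccine item from the multistate risk factors and from the yearly 2012-2022 strata in the Objectives. If it is wanted, there are two sound uses: a descriptive table among people with CLD who are alive and registered at the end of 2022, or a time-updated covariate in an analysis restricted to calendar time after third doses became available.

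Define flu vaccination either in a fixed window before CLD diagnosis (12 months, for example) or as a time-updated covariate with a calendar-time term, and not as ever/never over follow-up.

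Removing the COVID-19 item and dating flu vaccination before diagnosis change only wording in the Objectives, the Covariates section and the risk-factor list, with no new data collection. The time-updated options also require dated vaccination records and some extra modelling.
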